### Attrition and Adherence

Attrition will be considered under the following conditions: (a) two consecutive or three alternating absences from treatment sessions in a one-month period; (b) the inability to complete the post-test and follow-up; and (c) the development of any disabling condition preventing the participant’s participation in the study. Regarding adherence strategies, sessions missed until the established limit will be reset the following week. Flexible therapy hours will also be offered, and the relatives of the patients will be directly contacted by telephone to confirm the dates of evaluation, thereby reinforcing treatment adherence (Brunoni et al., 2011). Additional measures to avoid dropouts will also be applied, including periodic assessments of treatment satisfaction, discussion of difficulties in continuing treatment (for example, logistics of the trips to the laboratory) and attempts to resolve and avoid possible problems that may affect adherence to and continued participation in the study.

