### Sample Size

The sample size was estimated based on previous studies that used paired tDCS groups in treating AD (Ferrucci et al., 2008; Boggio et al., 2012). The power calculations determining the number of participants in each group were made in relation to the expected change in ADAS-Cog because this instrument is commonly used in studies involving cognitive evaluation in these patients (Vellas et al., 2007; Balietti et al., 2017; Xiao et al., 2017).

The expected significant improvement is reaching 3.76 points in the mean, with an standard deviation (SD) of 1.32 points, according to Rabey et al. (2013). Therefore, a calculation considering the level of *p* < 0.05 and 90% power as significant suggests that at least 10 patients would be necessary in each group to detect whether the difference found matches the effect of the active or simulated treatment. Considering the application of tDCS in multiple areas, stimulation time and the possibility of sample losses throughout the study (dropout, inability to continue treatment, death), 25 patients per group will be included, totaling 100 participants.

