Considering the different evaluations with the same cognitive tests throughout the clinical trial, the improvement in the performance of these tests may result from practice and not from the intervention applied (Chelune, 2010; Goldberg et al., 2015). A RCI will be used; it serves to assess whether the changes identified comparing pre- and post-intervention data can be attributed to the procedures used or are mere oscillations, artifacts, or measurement errors (Jacobson and Truax, 1991) resulting from repeated practice effects (Chelune et al., 1993). The RCI, correcting for practice effects and using the Iverson’s standard error of the difference will be calculated based on the Duff’s (2012) formulae.

The follow-up analysis will calculate the primary outcome (i.e., a decline in cognitive state). As proposed in Phase 1, the same cutoff will be used to classify clinical improvement (3.76 points in the mean, with an SD of 1.33 points in the ADAS-cog). The primary outcome measure will be calculated considering the differences between clinical improvement and clinical relapse (or censored if relapse did not occur). Kaplan-Meier survival analysis will be used to calculate this outcome. To investigate interactions of risk factors, the following variables will be observed: demographics characteristics (age, gender, level of education), clinical condition (duration of illness, comorbidities and neuropsychiatric states) and “methodological” variables (Phase 1 group and crossover). The hazard ratio will be estimated using the Cox proportional hazards (to each predictor variable or covariate)”

Regarding safety, adverse effects will be analyzed in terms of the ratio in each group and period (before and after treatment) and analyzed using Fisher’s exact test. Multivariate regression will be used to identify predictors of response. The outcome variables will be tDCS and cognitive intervention, and the predictors will be age, gender, comorbidities and use of medication.

The effectiveness of the blinding will be analyzed by using the chi-square test, comparing the ratio between errors and correct responses. Furthermore, these tests will be compared between patients with clinical response and those who failed to improve.

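### The follow-up survival analysis has only relapse or censoring, so responders who leave because they are declining are censored without observed relapse, and durability may be overstated

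*Protocol article*

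**What the plan says.** All references are to the protocol article.

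- **Endpoint** (Proposed Analysis): "The follow-up analysis will calculate the primary outcome (i.e., a decline in cognitive state".
- **Status rule** (same section): the outcome is calculated "considering the differences between clinical improvement and clinical relapse (or censored if relapse did not occur". No other status is given.
- **Estimators**: "Kaplan-Meier survival analysis will be used to calculate this outcome", and "The hazard ratio will be estimated using the Cox proportional hazards".
- **Foreseen exits**: Attrition and Adherence counts as attrition "the development of any disabling condition preventing" participation, inability to complete the post-test and follow-up, and a set number of missed sessions. Sample Size allows for "the possibility of sample losses throughout the study (dropout, inability to continue treatment, death".
- **Dropout handling**: Proposed Analysis promises intent-to-treat and a sensitivity analysis chosen from last observation carried forward, complete cases, likelihood methods and multiple imputation. It does not connect these to the survival analysis.
- **Who is followed** (Stepwise Procedures): responders to active tDCS from phases I and II, for one year of maintenance.

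**The concern.** Kaplan-Meier treats a censored patient as having the same later relapse risk as the patients still under observation. That is reasonable for someone who moves away. It is doubtful for a patient with a progressive dementia who can no longer attend, because the reason for leaving may be the cognitive decline that the endpoint is meant to capture. Under the only rule written, that patient leaves the risk set without an event.

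The issue goes beyond detail left to an analysis plan, because the article itself fixes the event, the censoring rule and the estimator. The dropout methods listed do not repair it. None is an informative-censoring or competing-event method, and carrying forward a responder's last improved score would push in the same direction. What is at stake is the article's time-to-relapse evidence on whether benefit is sustained under maintenance tDCS.

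**Working it through.** **Inputs.** The documents give the rule, the endpoint and the kinds of exit. They give no 12-month relapse rate, exit rate, or link between exit and decline, and no planned figure for this analysis that could be reproduced. Those quantities are assumed below. The ADAS-Cog schedule in follow-up is also unclear: maintenance blocks are every other month, assessments are repeated in all steps, and the ANOVA names only the 12-month point. Both schedules are shown.

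**Model A: some relapsing patients leave before the visit that would show it.**
Let p be true 12-month relapse, m the number of equally spaced visits, q = 1 − (1 − p)^(1/m) the relapse risk per interval, and f the share of relapsing patients who leave before detection. Of those at risk at the start of an interval, 1 − qf are present at the visit and q(1 − f) are seen to have relapsed. The Kaplan-Meier step is q(1 − f)/(1 − qf), so

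reported relapse = 1 − (1 − p)/(1 − qf)^m.

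For p = 0.5 and m = 6, q = 1 − 0.5^(1/6) = 0.1091. With f = 0.2 the result is 1 − 0.5/(0.9782)^6 = 0.43.

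| True relapse | Visits | f = 0.2 | f = 0.3 | f = 0.5 |
|---|---|---|---|---|
| 50% | two-monthly | 43% | 39% | 30% |
| 50% | month 12 only | 44% | 41% | 33% |
| 40% | two-monthly | 34% | 30% | 23% |

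A simulation of 400,000 patients agrees (0.430, 0.390 and 0.301 for the first row). If the decline-related leavers are counted as relapses, the step becomes q(1 − f) + qf = q, and the true p is recovered.

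**Model B: leaving is not tied to a relapse that has already happened.**
Let R be 12-month relapse among stayers, D the 12-month exit probability, h = −ln(1 − R), c = −ln(1 − D), and k the ratio of relapse hazard after exit to that of stayers. Kaplan-Meier with exits censored gives e^(−h) = 1 − R. Had leavers been followed, the relapse-free share would be

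e^(−(h+c)) + c·e^(−kh)·[1 − e^(−(c+h−kh))]/(c + h − kh).

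For R = 0.3, D = 0.2 and k = 2: h = 0.3567, c = 0.2231, and 0.560 + 0.117 = 0.677.

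| Relapse-free at 12 months, R = 30% | D = 20% | D = 40% |
|---|---|---|
| Kaplan-Meier, exits censored | 70.0% | 70.0% |
| Leavers followed, k = 0.5 | 71.4% | 72.9% |
| Leavers followed, k = 1 | 70.0% | 70.0% |
| Leavers followed, k = 2 | 67.7% | 65.2% |
| Leavers followed, k = 4 | 64.4% | 58.4% |
| Every exit counted as failure | 56.0% | 42.0% |
| Every exit a competing event (1 − cumulative incidence) | 72.9% | 76.2% |

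For exits of 10% to 40% and k of 2 to 4, durability is overstated by 1.1 to 11.6 points at R = 30% and by 1.4 to 12.3 points at R = 50%. A shared-frailty simulation (true relapse-free share 60%, frailty variance 0.5 to 1) gives roughly 1 to 5.5 points.

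**The case against.** **Direction.** A reader might infer that the curve is certainly too favourable. The documents do not support that. They never say leavers are declining, they count missed sessions as attrition, and they name transport and personal difficulties as reasons for absence. The cohort is mild-stage, and Phase III takes only responders. At k = 1 there is no bias, and at k = 0.5 it reverses. Model A also builds in its direction, because only relapsing patients leave. This objection stands, so the claim has to be conditional.

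**Status of leavers.** A reader might also infer that leavers count as successes. They do not: censoring removes them from the risk set without observed relapse.

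**Cox model.** A further tempting inference is that the hazard ratios for covariates such as age or comorbidity are pulled towards no effect. With a true hazard ratio of 2.0 and the same f in both covariate groups, simulated estimates stay close to 2. Attenuation, to about 1.29, appears only if f is also assumed to differ by covariate (0.2 against 0.5). Nothing in the documents supports that assumption.

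**Remedy.** Counting every exit as failure can be further from the truth than the present rule. At R = 30%, D = 20% and k = 2, Kaplan-Meier errs by 2.3 points and the composite by 11.7 (67.7 − 56.0). It also changes the endpoint from cognitive decline to something broader. This defeats a broad composite as the main analysis. It does not defeat counting only withdrawals documented as decline.

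**Level of detail.** Status by reason for leaving is often left to an analysis plan. Here, however, the article states a two-status rule for this endpoint, and the rule as stated can give a biased curve.

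**Conclusion.** The point holds conditionally. The article fixes one censoring rule for an endpoint of cognitive decline, foresees exits that may themselves be decline, and links no sensitivity analysis to that rule. If some responders leave maintenance because they are declining, Kaplan-Meier may overstate durability. Under Model A's assumptions a true 12-month relapse of 50% would be reported as 43% to 30%. Under the looser link of Model B or shared frailty the overstatement runs from about 1 to 12 points. It is nil if leavers relapse like stayers. All of these figures rest on assumed relapse rates, exit rates and visit schedules. For death the direction depends on the estimand: as a competing event, the share never relapsing is higher than the Kaplan-Meier figure. The plan should be changed, with moderate confidence in the practical effect.

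**What to change.** In the follow-up part of Proposed Analysis:

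1. Record a coded reason for leaving, and seek an ADAS-Cog at exit whenever the patient can be tested.
2. Count withdrawal documented as due to cognitive or functional decline as relapse.
3. Keep unrelated exits (logistics, missed sessions, moving away) censored.
4. Treat death and disabling conditions not due to Alzheimer's disease as competing events, reported by cumulative incidence.
5. As sensitivity analyses, report a composite of relapse or any such exit, and the version using ADAS-Cog relapse only.

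**Cost:** slightly more analysis work, one coded field and an exit assessment where feasible, with no new patients. Coding the reason needs judgement, preferably by someone blind to phase I group. The relapse rate may look less favourable.

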Accordingly, we propose that stimulating different brain regions specifically related to the neuropathology of AD along with repeated applications of 10-min tDCS in each session may be an option to achieve short- and long-term effects. However, at this time we have only just drawn up a study protocol and these hypotheses can only be tested in the main clinical trial that we aim to perform. In addition, no reports of factorial randomized clinical trials using with tDCS and cognitive intervention stimulating different cortical regions with a 10-min interval in each, and with follow-up for AD-related outcomes have been found to date.

In this way, we designed the Neurostimulation combined with Cognitive Intervention in AD (NeuroAD) clinical study, a phase II/III trial, to address the safety and efficacy of tDCS and cognitive intervention in the treatment of AD. Based on the aforementioned data, which suggest beneficial effects of both cognitive intervention and tDCS on patients with AD, we hypothesize that combining both treatments modulates cortical activity and improves the long-term clinical symptoms of patients, manifested as increased cognition and functional capacity and reduced affective and behavioral changes.

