### Randomization and Blinding

The participants will be randomized into 1:1:1:1 blocks using the random number generator of an open-access randomization software program^1^. This sequence will be remotely performed by a blind researcher not involved in other research procedures. After the randomization process, a blinded staff member will perform patient allocation between the groups. Hidden allocation will be performed with closed, sealed and sequentially numbered envelopes. The participants will be identified by codes and will also be blinded; that is, they will ignore the arm of the study to which they will be allocated. The evaluation and treatment will be performed by independent researchers, who will identify the patients by their respective codes and will be blinded to the other research procedures. Data analysis will be performed by a professional not involved in any stage of patient recruitment, screening, assessment, or intervention. The effectiveness of the masking will be assessed after completing the treatment by interviewing the raters, who will be asked what type of treatment (active or placebo) they believe that the patient received. The relatives of participants will also be blinded and asked, at the end of the treatment, to which group they believe that the patient was allocated. The patients will also be asked questioned about which group they believe have been allocated. We decided to assess the effectiveness of the blinding by asking the relatives and/or caregivers of the patients because the patients have mild AD.

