#### Proposed Analysis

Intent-to-treat analysis will be used; that is, all participants will be included in the analysis, including those who drop out before completing the treatment. However, high or different rates of dropouts between the treatment arms may lead to biases. Thus, a sensitivity analysis will be performed with different assignment procedures to assess the value of the data. The best strategy resulting from the following methods will be chosen: last observation carried forward, complete case analysis, likelihood-based methods, or multiple imputation.

Descriptive statistics will be used to describe clinical and sociodemographic characteristics and the primarily and secondary outcomes of each group at the baseline. The groups will be compared by analysis of variance (ANOVA), for continuous variables, or the chi-square test, for categorical variables.

The primary outcome will be examined by split-plot ANOVA with one dependent variable (ADAS-Cog score) and two independent variables, namely, one intra-group variable and one inter-group variable. The within-subject variable will include time (baseline, post-treatment and 12-month follow-up), and the effects of the treatment condition (active or placebo tDCS; active or placebo cognitive intervention) will be examined as a between-groups variable. *Post hoc* comparisons using Bonferroni correction will be performed where appropriate. Finally, the effect sizes regarding inter-group comparisons will be calculated using the eta squared (*η*^2^), and effect sizes regarding intra-group comparisons will be calculated by means of Cohen’s d using Hedges’ correction (Fritz et al., 2012), adopting the significance level of *p* < 0.05. For all variables of the secondary outcomes, the same analysis strategy will be used. Non-parametric tests will be performed if some of the outcomes do not meet the conditions necessary for parametric analysis.

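### Safety is a stated aim, but the only inferential rule fixed for it is a by-group Fisher's exact test at 25 per group, which is too weak to support a safety conclusion

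*Protocol article*

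**What the plan says.** The Introduction of the protocol article describes the trial as designed "to address the safety and efficacy of tDCS and cognitive intervention in the treatment of AD". Under Safety, participants are asked about adverse effects at the end of every session, and each effect is scored for intensity (1 to 4) and for relatedness to stimulation (1 to 5).

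Under Proposed Analysis, the rule for these data is that "adverse effects will be analyzed in terms of the ratio in each group and period (before and after treatment) and analyzed using Fisher’s exact test". No other inferential rule for safety appears in the article.

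Under Sample Size, the power calculations "were made in relation to the expected change in ADAS-Cog", and "25 patients per group will be included, totaling 100 participants". Under Randomization and Blinding, "The participants will be randomized into 1:1:1:1 blocks". The factorial margin for tDCS is therefore 50 active against 50 sham.

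**The concern.** A significance test of no difference answers a safety question only when it rejects. When it does not reject, its value depends on how large an excess it could have found. Here the number of patients was chosen for a continuous efficacy scale, and the safety test is specified by group, so each pairwise comparison has 25 patients per side. If such a test has little chance of detecting an excess that would matter, a non-significant p-value says almost nothing about safety.

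The Introduction states that no factorial trial of this combination over several cortical regions with follow-up has been reported. Inference about its tolerability should therefore show what excess the data can and cannot exclude.

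**Working it through.** **The plan's own design figure.** The only sample-size result in the article is for ADAS-Cog: "The expected significant improvement is reaching 3.76 points in the mean, with an standard deviation (SD) of 1.32 points", and "90% power as significant suggests that at least 10 patients would be necessary in each group". The standardized difference is 3.76 / 1.32 = 2.85. The normal approximation gives n = 2 × (1.96 + 1.2816)² / 2.85² = 2.6, so 3 per group, and the t-test gives 4. The stated 10 is not reproduced, but it is worded as a minimum and has no bearing on safety. There is no corresponding figure for adverse effects.

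**Inputs for the safety check**
- Group size 25, or 50 per side on the tDCS margin (Sample Size; Randomization and Blinding).
- Significance level 0.05. Proposed Analysis states "adopting the significance level of *p* < 0.05" for the efficacy analyses; it is assumed here for Fisher's test, two-sided.
- Comparison: two groups at a time, with one yes/no outcome per patient (assumption).
- Adverse-effect rates: not given, so assumed over a range.
- Dropout: no rate given; 0% assumed, 20% as sensitivity.

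**Method.** With X ~ Bin(n, p_active) and Y ~ Bin(n, p_sham), power is the sum of P(X = x) × P(Y = y) over all tables in which Fisher's two-sided p is below 0.05 and the active proportion is the higher one.

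| Sham v active | 25 v 25 | 50 v 50 |
|---|---|---|
| 2% v 15% | 12% | 51% |
| 5% v 15% | 7% | 24% |
| 5% v 20% | 20% | 51% |
| 10% v 20% | 9% | 20% |
| 10% v 30% | 31% | 64% |
| 20% v 40% | 23% | 52% |
| 30% v 50% | 23% | 46% |
| 10% v 40% | 59% | 93% |
| 30% v 60% | 51% | 83% |

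With 20% dropout, 10% v 30% falls from 31% to 24% (20 v 20) and from 64% to 53% (40 v 40).

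**What rejection requires.** With no events on sham, 5 of 25 on active gives p = 0.0502 and 5 of 50 gives p = 0.056. Significance needs 6 events in either case: 24% of a group of 25, or 12% of a group of 50.

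**What an interval adds.** With 5 of 25 on active and 1 of 25 on sham, p = 0.19. The Newcombe 95% interval for the difference is about −3 to +35 percentage points. The p-value does not show that the data leave an excess of a third of patients open.

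**Zero events.** The exact one-sided 95% upper limit is 1 − 0.05^(1/n). For n = 25 it is 11.3%; for n = 50 it is 5.8%.

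**The case against.** The strongest objection is that the article never says a non-significant test will be taken as showing safety. That is correct. A reader might infer it, because the article elsewhere describes tDCS as a safe technique. But Proposed Analysis contains no rule for interpreting p above 0.05 and no criterion for declaring the regimen safe, and Anticipated Results draws no safety conclusion from a test. The point here is limited to what the stated test can support.

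Second, a reader might infer that a relevant excess would usually be missed. The documents do not support that in general. No event rates are given, and on the 50 v 50 margin the three main scenarios are detected slightly more often than not. A 30-point excess is found in 83% or more of trials there, and in just over half even at 25 v 25. The low figures belong to the by-group comparison, which is the natural reading of the stated rule, and to excesses of up to about 20 points.

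Third, intervals may stand in a full protocol or analysis plan that is not shown, and the by-group proportions will in any case be described. So the absence of intervals is not the finding. What remains is that the article does choose a method for a stated aim, and the chosen by-group test is a weak one when the design offers a better comparison.

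Fourth, sizing a trial on its primary efficacy outcome is ordinary practice. That is accepted; it explains the low power and is not itself an error.

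**Conclusion.** The point holds in this limited form. For a stated safety aim, the only inferential rule fixed in the article is a by-group Fisher's exact test. At 25 per group that test detects excesses of 13 to 20 points in about 12% to 31% of trials in the three main scenarios (2% v 15%, 5% v 20%, 10% v 30%). A non-significant result could not carry a safety conclusion. Pooling over the cognitive factor raises detection in the same scenarios to 51% to 64%, which is better but still leaves the p-value alone insufficient.

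These figures rest on assumed event rates, a two-sided 0.05 level, complete data and pairwise comparison. This is an improvement that should be made, not a contradiction in the plan.

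**What to change.** - Make the main safety analysis the per-patient risk difference for active against sham tDCS, pooled over the cognitive factor (50 v 50), with a 95% confidence interval. Report it for any effect of moderate or strong intensity and for discontinuation due to an effect.
- Give the exact upper confidence limit for serious events among the patients on active tDCS. With none in 50, this is 5.8% (one-sided 95%).
- State that any safety conclusion is drawn from these limits, and that a non-significant Fisher test is not evidence of safety.
- Keep the by-group Fisher test as descriptive.

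The per-session records of effects, intensity and relatedness are already planned, so no patients or procedures are added. The cost is analysis-plan wording, a few extra intervals and a more modest safety claim.

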### Safety

To investigate adverse effects, the participants will be asked at the end of each session whether they experienced effects such as “tingling”, “burning”, “headache”, “somnolence”, among others and subsequently asked the intensity of this sensation (1—none, 2—mild, 3—moderate, 4—strong) and whether this effect could be related to stimulation using a Likert scale ranging from 1 (unrelated) to 5 (strongly related). Although tDCS is considered a safe technique that has been applied to several neurological and psychiatric disorders for years (Nardone et al., 2015), if the patient exhibits any severe impairment or discomfort, treatment will be discontinued, and medical assistance and physical and psychological therapy will be provided to control potential problems and promote recovery.

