Each aforementioned area will be stimulated for 10 min, totaling 30 min of treatment (three areas stimulated per session). The reference electrode 35 cm^2^ (5 × 7 cm) will be placed in the contralateral supraorbital area. The placebo stimulation protocol will be identical, although the device will cease to emit a current 30 s after starting the stimulation. Thus, the active current is simulated (slight tingling and itching sensation) for a short period, and the effects disappear shortly after the start of the stimulation (Nitsche et al., 2003; Gandiga et al., 2006).

An *fMRI* of all participants will be obtained before the experiment. The FSL software (FMRIB’s Software Library, University of Oxford, UK) will be used to transform coordinates for brain areas for each subject individually. The individual structural images will be initially converted into MNI coordinates (standard Montreal Neurological Institute) and then the MNI coordinates will be inversely transformed to the original imaging space. These values will be obtained by converting Talairach coordinates to the MNI space (Paus, 1996). These coordinates will be used to guide the frameless stereotaxy (Brainsight system, Rogue Research, Montreal, QC, Canada). The location of target regions will be performed by an experienced and trained professional. Procedures will be repeated at each treatment session for all participants involved.

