**Figure 2 F2:**
[figure not shown]
Flowchart of phases I (double-blind factorial clinical trial), II (crossover) and III (follow-up) of the Neurostimulation combined with Cognitive Intervention in Alzheimer’s disease (AD) Study (NeuroAD). T0: Baseline, pre-intervention measurement. T1–T8: intervention, tDCS and cognitive treatment. T9: endpoint, post-intervention measurement.

The phase I is a double-blind, randomized, factorial clinical trial in which tDCS will be applied in parallel to cognitive intervention in AD patients. This stage includes two measurement time points: baseline (week 0) and post-treatment (week 8). The data collection sessions will be performed by treatment-blinded investigators including the primary and secondary outcomes assessments. The pre-measurement consists of a screening and measurement part. The screening part contains data of the DSM-IV-TR, NINCDS-ADRDA criteria, CDR, MMSE and health questionnaire (including questions about disease duration, comorbidities and use of medication). Adverse effects will be assessed at each session, wherein the tDCS rater will ask the patients whether they feel any discomfort or pain and whether this could be related to tDCS.

Phase II is an open-label, crossover phase in which non-responders from groups (2) and (4) (i.e., those receiving sham tDCS) receive a course of active tDCS using the same parameters and montage of phase I, that is, a direct current of 2 mA (current density = 0.13 mA/cm^2^) for 30 min/day for 24 days, in respective six brain regions.

Phase III is the longitudinal study of NeuroAD in which all active-tDCS responders—that is, responders from groups (1) and (3) from phase I and responders from phase II will be enrolled in a bi-monthly 1-year follow-up. Thus, two months after the last session, the participants will receive ten consecutive tDCS sessions (from Monday to Friday), which will be repeated every other month, until completing a one-year period (totaling 70 follow-up sessions). The tDCS parameters will be the same as those applied during the period between baseline and post-treatment, and the same cortical areas will be stimulated.

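### The stated safety analysis, a ratio per group with Fisher's exact test, uses neither the intensity and relatedness grades nor the repetition over 24 sessions, and can lose the active-versus-sham contrast for common sensations

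*Protocol article*

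**What the plan says.** All of this is in the protocol article.

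- **Collection.** Under Safety, "the participants will be asked at the end of each session whether they experienced effects such as" tingling, burning, headache, somnolence and others. Stepwise Procedures repeats the frequency: "Adverse effects will be assessed at each session, wherein the tDCS rater will ask the patients". The tDCS section sets 24 sessions.
- **Grading.** Under Safety, patients are "asked the intensity of this sensation (1—none, 2—mild, 3—moderate, 4—strong"), and relatedness is rated "using a Likert scale ranging from 1 (unrelated) to 5 (strongly related").
- **Sham.** The device stops emitting current after 30 s, so that "the active current is simulated (slight tingling and itching sensation) for a short period" (Intervention, tDCS).
- **Analysis.** Under Proposed Analysis, "adverse effects will be analyzed in terms of the ratio in each group and period", the periods being "before and after treatment) and analyzed using Fisher’s exact test".

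The Introduction names safety as one of the trial's two aims. The Sample Size section gives 25 patients per group. No expected adverse-effect rate is given anywhere.

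**The concern.** The article names a summary (a ratio), the strata (group and period) and a test (Fisher's). None of the three uses intensity, relatedness or the number of sessions affected, although these are what could show that full-length current is felt more strongly or more often than a 30 s current.

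The counted event and the unit are not stated, and both natural units cause trouble.

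- **Patients with any effect.** Over 24 sessions a common sensation accumulates to nearly everyone. For tingling and itching, which sham is built to produce, the two arms then look alike for a reason unrelated to tolerability.
- **Sessions.** Repeated reports from one patient are treated as independent.

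The before/after split also does not match the collection. Effects are recorded during treatment, at each session, and no pre-treatment recording of them is described.

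At stake is how a null result would be read. A non-significant Fisher test could be reported as good tolerability when the grades already collected might show otherwise.

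**Working it through.** The article gives no safety rate, power or sample size, so there is no figure of its own to reproduce.

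**Inputs from the article:** 24 sessions; 25 per group, hence 2 × 25 = 50 active and 50 sham tDCS when pooled over the cognitive factor; intensity grades 1 to 4. **Assumed:** per-session rates, within-patient correlation ρ, intensity distributions, two-sided 5% level.

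**1. Patient as unit, any effect.** With independent sessions, P(ever) = 1 − (1 − p)^24. For example, p = 0.20 gives 1 − 0.80^24 = 99.5%, and p = 0.10 gives 1 − 0.90^24 = 92%.

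With correlated sessions (beta-binomial), P(ever) = 1 − B(a, b + 24)/B(a, b), where a = p(1/ρ − 1) and b = (1 − p)(1/ρ − 1). Fisher power is exact. Power for the rank test on the number of affected sessions is simulated (3,000 runs, standard error at most √(0.25/3000) = 0.9 points).

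| ρ | Per session, active v sham | Ever affected | Fisher, any effect | Rank, affected sessions |
|---|---|---|---|---|
| 0.1 | 50% v 30% | 99.9% v 98.1% | 0% | 100% |
| 0.1 | 40% v 20% | 99.6% v 92.3% | 16% | 100% |
| 0.1 | 30% v 15% | 98.1% v 85.0% | 53% | 100% |
| 0.1 | 20% v 10% | 92.3% v 71.2% | 73% | 98% |
| 0.3 | 50% v 30% | 97.0% v 86.3% | 33% | 95% |
| 0.3 | 40% v 20% | 93.4% v 72.4% | 75% | 98% |
| 0.3 | 30% v 15% | 86.3% v 61.5% | 76% | 92% |
| 0.3 | 20% v 10% | 72.4% v 46.7% | 70% | 81% |

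Rarer effects, same method:

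| ρ | Per session, active v sham | Fisher, any effect | Rank, affected sessions |
|---|---|---|---|
| 0.1 | 10% v 5% | 68% | about 83% |
| 0.1 | 5% v 2% | 67% | about 77% |
| 0.3 | 10% v 5% | 47% | about 59% |

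Stronger clustering also weakens the ceiling: at 40% v 20% and ρ = 0.5, 81% v 55% are ever affected and Fisher has 77% power.

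If single groups of 25 are compared instead, Fisher has less power. With independent sessions, 40% v 20% gives 0%, 20% v 10% gives 1% and 10% v 5% gives 37%.

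**2. Session as unit.** There are 50 × 24 = 1,200 sessions per side. The variance is inflated by 1 + 23ρ, which is 3.3 at ρ = 0.1 and 7.9 at ρ = 0.3. The approximate false-positive rate of a nominal 5% test is 2[1 − Φ(1.96/√(1 + 23ρ))]:

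- ρ = 0.1: 1.96/1.817 = 1.079, about 28%
- ρ = 0.3: 1.96/2.811 = 0.697, about 49%

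Simulating Fisher's test with no true difference gave 26 to 28% and 47 to 49%.

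**3. Using the grade.** Assumed worst intensity (none/mild/moderate/strong), 50 v 50, 4,000 runs:

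| Sham | Active | Fisher, any | Fisher, moderate or strong | Mann-Whitney on grade |
|---|---|---|---|---|
| 5/65/25/5% | 5/35/45/15% | 1% | 82% | 81% |
| 60/25/10/5% | 35/30/25/10% | 66% | 57% | 78% |

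In the first row both arms are at 95% for any effect, and only the grade separates them. In the second there is no ceiling and the gain from ranking is modest. A severity cut-off alone loses power there.

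**The case against.** A reader might infer that the active-versus-sham comparison is bound to hit a ceiling. The article does not support that, for four reasons.

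- It does not say that the ratio means any effect ever per patient. A ratio per symptom, or above an intensity level, need not saturate.
- It gives no adverse-effect rate. Near-zero power belongs to the common-effect, weak-correlation corner of an assumed grid; five of the eight common-rate scenarios give Fisher 53 to 76%, excluding the three at 0, 16 and 33%.
- Sham is said to imitate only slight tingling and itching, briefly. Nothing says that it reproduces burning, headache or somnolence.
- This is a condensed article. The event definition and severity cut-offs may sit in an analysis plan that is not shown, and Fisher's test on adverse-effect proportions is a usual choice.

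A further objection concerns the remedy. A raw count of affected sessions would flatter patients who stop early because of a bad effect. The Attrition and Safety sections both foresee patients leaving treatment.

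These points limit the claim about size and shape the remedy. They do not remove the defect. The article commits to a summary, strata and a test, and as stated these leave out graded, repeated data on a declared aim. The mismatch between the before/after periods and per-session collection is also in the text itself.

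**Conclusion.** The point holds in limited form. The stated safety analysis discards the intensity grades, the relatedness grades and the repetition, and its periods do not fit when effects are recorded.

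Under the assumed common rates (sham 10 to 30% per session, active 20 to 50%, ρ 0.1 to 0.3, 50 v 50), any-effect Fisher has about 0 to 76% power against 81 to 100% for a rank test on affected sessions. For rarer effects the difference shrinks to roughly 10 to 15 points. If sessions are counted, a nominal 5% test runs at about 26 to 49%.

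The direction follows from the design. The size depends wholly on rates and correlations that the article does not give. It is worth correcting before unblinding, but it does not threaten the trial.

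**What to change.** Rewrite the safety analysis with the patient as the unit and, for each symptom:

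1. Compare active with sham tDCS on worst intensity, by a rank or ordinal test.
2. Compare the proportion of attended sessions with intensity 2 or more, or use a count model with sessions attended as offset, so that early stoppers do not look tolerant.
3. Keep Fisher's test for patients with any effect rated 3 to 4 and, separately, for effects rated 4 to 5 related.
4. Replace the before/after periods with the treatment sessions.
5. Report absolute incidence in active-tDCS patients with a 95% CI, because for tingling and itching sham is not a no-sensation control.

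The cost is wording and a few more safety tables; all the data are already to be collected. The added comparisons raise multiplicity, so they should be read descriptively.
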